#### Stress Reactivity

2.9.3

To examine links between fear generalization and HPA activity, we will correlate CAR, quantified as area under the curve with respect to the increase (AUCi), which reflects HPA‐axis stress reactivity, with fear generalization. Fear generalization, measured via Linear Deviation Score (LDS), Mean Response across stimuli, and CS‐Differentiation, will be correlated with CAR to identify links between stress reactivity and fear learning. We will compare CAR between healthy adults and those with current or past mood disorders (anxiety or depression) and examine its relation to fear generalization. Lastly, we will use Pearson correlations to examine whether morning cortisol levels predict experiment‐induced HPA‐axis responses, using data from the follow‐up only as no similar probes were included in prior assessments.

#### Epi(genetic) Analyses

2.9.4

Genetic variations in candidate genes and the polygenic risk scores for ANX will be derived from the recent GWAS of the PGC consortium (Strom et al. 2024). These will be applied individually as predictors of fear generalization in multiple logistic regression models on parameters calculated from the experiment.

DNAm values in genes related to HPA‐system (CRH, CRHR1, PACAP, ADCYAP1, SGK1, NR3C1) will be correlated with fear generalization, childhood adversity and life events by linear regression analyses. EWAS analyses on fear generalization index will be applied in a subset of samples with complete fear generalization and environmental information over the different recruitment waves. Multiple logistic regression modelling will be used to determine the contribution of DNAm to fear generalization parameters and the above‐mentioned environmental factors.

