#### Stability of Fear Generalization Processes

2.9.1

To examine the stability of fear generalization, we will calculate established indicators and firstly adapt the approach outlined by Cooper et al. (2023). Linear mixed models with a fixed effect of stimulus for the acquisition phase and generalization will test differential fear conditioning. Furthermore, building on the approach by Cooper et al. (2023), additional models will be applied to examine mean‐level changes in fear responses over time. These models will include a random intercept for participants and random slopes for timepoint, as well as fixed effects of stimulus, phase (acquisition only), timepoint (T1, [T2,] FU), and their interactions. To investigate individual patterns of fear generalization, additional mixed‐effects models will be fitted to examine the effect of timepoint on the Linear Deviation Score (LDS). Age and the Age × Timepoint interaction will be included in all models to account for variability in the interval between the initial assessment and follow‐up, as well as cohort‐related age differences. As age effects are not central to the present research question, they will not be considered further. A more fine‐grained modeling of temporal variability will be implemented in the prediction analyses (see below *Prediction of anxiety symptomatology*).

Next, we aim to replicate the variance component analysis based on the principles of generalization theory to examine how variance is distributed across different levels of the model and to evaluate the relative contributions of individual differences, stimuli, and sessions to the observed effects (Cooper et al. 2023).

Further, we will assess intraindividual stability (i.e., within‐subject stability of response patterns) and change (i.e., within‐subject reliability of change) using the coefficients *R*
_IRS_ and *R*
_C_. *R*
_IRS_, as used by Torrents‐Rodas et al. (2014), quantifies the proportion of within‐person variance in stimuli responses that remains stable across time. This measure is well‐suited to capture stability of generalization patterns, as it isolates the consistency of individual differences in response patterns over repeated sessions. To complement this, we will also calculate the *R*
_C_ coefficient (Cooper et al. 2023), which measures the reliability of change in responses across individuals between timepoints. It quantifies how much non‐stable variance in responses reflects changes over time. Larger *R*

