_C_ suggest reliable tracking of systematic changes in response patterns across sessions.

We will also calculate Intraclass Correlation Coefficients (ICCs) to assess response consistency. Beyond Cooper et al. (2023)'s stimulus‐specific ICCs for acquisition and generalization phases, we will include three additional indices (Stegmann et al. 2019): ICCs based on the Linear Deviation Score, the Mean Response across all stimuli, and CS‐Differentiation, enabling interpretation of individual response patterns during generalization.

To investigate age‐related trajectories of fear generalization, we will apply likelihood‐based linear mixed models in the combined child, adolescent and adult samples depending on resulted estimates (Mallinckrod et al. 2008). This approach allows joint analysis of all timepoints based on a multivariate model useful to analyse longitudinal continuous outcomes.

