#### Prediction of Anxiety Symptomatology

2.9.2

For exploratory prediction analysis, we will compute an *Anxiety Factor Score*, yielding a single, streamlined, and reliable index of anxiety‐related psychopathology, based on Pittig et al. (2023), but using follow‐up‐based standardization. Each psychometric measure will be z‐standardized using the mean and standard deviation of the full sample at follow‐up and then averaged across anxiety‐related measures (i.e., BAI, PROMIS Anxiety, ASI‐3, PAS, SPAI, and PSWQ). Importantly, this composite reflects relative anxiety severity at follow‐up rather than intraindividual change over time.

To account for baseline differences in symptom levels, baseline anxiety will be included as a covariate in all longitudinal prediction models, thereby allowing the examination of predictors of follow‐up anxiety above and beyond initial symptom levels. Baseline anxiety will be operationalized as a composite score of anxiety symptomatology derived from the measures available at baseline, following the same general procedure as described above.

Next, linear mixed models expand the model of anxiety prediction and fear generalization with polygenic risk scores derived from publicly available Anxiety GWAS (Strom et al. 2024), cortisol awakening response (area under the curve of cortisol), early trauma and life events to explore each variable's contribution to anxiety. As described above, variability between time points will be included by modelling age as a quantitative variable and allowing for corresponding interactions with measurement timepoints. To further model this, we will also account for time‐warping in these analyses along the lines of the fdasrvf package in R (https://cran.r‐project.org/package=fdasrvf).

Moreover, random forest methods will integrate complex variables (e.g., GWAS and DNAm), combining multiple decision trees to obtain stable, accurate predictions via cross‐validation. Each tree votes, and the class with most votes determines the final classification. As predictors we will include fear generalization indices, psychometrics, life events, endocrine and molecular measures. Random forests resist overfitting, particularly under cross‐validation and with good predictive power. Besides, they handle missing data effectively, preserving predictive power.

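### Section 2.9.4 assigns logistic regression to fear-generalization scores that the rest of the plan treats as continuous, and defines no category or cut-point

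*Protocol article*

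**What the plan says.** All places are in the protocol article.

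- **Section 2.9.4, variants and polygenic risk scores:** "These will be applied individually as predictors of fear generalization in multiple logistic regression models on parameters calculated from the experiment".
- **Section 2.9.4, methylation:** "Multiple logistic regression modelling will be used to determine the contribution of DNAm to fear generalization parameters", and to the environmental factors named earlier in that section.
- **Section 2.9.4, a little before that sentence:** methylation in HPA-related genes "will be correlated with fear generalization, childhood adversity and life events by linear regression analyses".
- **Section 2.9.3, what the parameters are:** "Fear generalization, measured via Linear Deviation Score (LDS), Mean Response across stimuli, and CS‐Differentiation". These are correlated with the cortisol awakening response.
- **Section 2.9.1:** mixed-effects models take the Linear Deviation Score as outcome, and intraclass correlations are planned for all three indices. Age trajectories of fear generalization use linear mixed models, described as a "multivariate model useful to analyse longitudinal continuous outcomes".
- **Section 2.9.2, prediction of anxiety:** the only outcome defined is the Anxiety Factor Score, an average of six z-standardized scales. The random forest is then described thus: "Each tree votes, and the class with most votes determines the final classification". No class is named.

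**The concern.** Logistic regression models the probability of a category. The three fear-generalization indices are numeric scores, and outside section 2.9.4 every analysis of them is one for a continuous variable. An analyst who follows section 2.9.4 as written must first turn each score into groups, and the article does not say how.

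Two things are at stake. Grouping a continuous score discards information, which matters for genetic and methylation effects if these are small. It also adds a free choice, the cut-point, to a set of models that already covers several indices and many predictors.

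The forest raises a milder form of the same question. A vote among classes does not produce a prediction of a continuous score, and the continuous score is the only outcome that section 2.9.2 defines.

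**Working it through.** The article gives no sample-size calculation, significance level or power for these models, so there is no stated figure to reproduce. The check has three steps.

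**1. Can the model be fitted as stated?** A binary logistic model was tried on a simulated continuous (normal) outcome. The software refused it because the outcome must lie between 0 and 1. A grouping step is therefore needed, and none is described. Section 2.8.3 does mention dimensional and categorical levels, but for anxiety phenotypes, not for the fear-generalization parameters.

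**2. What would one binary cut cost?** Assume a roughly normal score, a small effect, and a cut that puts a proportion p in one group. The efficiency relative to linear regression on the uncut score is

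E = φ(z_p)² / [p(1 − p)],

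where φ is the standard normal density and z_p the normal quantile at p.

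| Split | E | Information lost |
|---|---|---|
| 50/50 | 0.3989² / 0.25 = 0.637 | 36.3% |
| 40/60 | 0.622 | 37.8% |
| 33/67 | 0.595 | 40.5% |
| 25/75 | 0.3178² / 0.1875 = 0.539 | 46.1% |
| 20/80 | 0.490 | 51.0% |
| 10/90 | 0.342 | 65.8% |

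The median split is the best case, so about 36% is the minimum under these assumptions.

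In terms of power, assume a two-sided 5% level and an effect that linear regression detects with 80% power. Power after the cut is Φ(√E × (1.960 + 0.842) − 1.960):

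- Median split: √0.637 = 0.798; 0.798 × 2.802 − 1.960 = 0.276; power about 61%.
- Top-quartile cut: √0.539 = 0.734; 0.734 × 2.802 − 1.960 = 0.097; power about 54%.

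A simulation of 3,000 runs (583 people, correlation 0.116) gave 80%, 61% and 54% for linear regression, median split and top-quartile cut.

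**3. How far does the figure depend on the assumptions?**

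- An ordinal model with three equal groups has E = 0.793, a loss of 20.7%.
- For a median split of a non-normal score, E = 4 f(m)² σ², where f(m) is the density at the median and σ² the variance. This gives 0.96 for a t distribution with 5 degrees of freedom, 1.0 for an exponential, 2.0 for a Laplace and 0.33 for a uniform distribution. With heavy tails or strong skew the loss can be small or absent; with a flat distribution it is larger.

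The 36% figure therefore applies to a single cut of a roughly normal score. The linear models that the plan itself uses for these indices make a similar distributional assumption.

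**The case against.** **The word may simply be loose.** The authors may intend ordinary linear models, and then no information is lost. That is quite possible, and it is why the loss is stated as conditional. But logistic is written twice, and the stated model does not fit the stated outcome. The reservation in section 2.9 that analyses may be adjusted for new methods or data quality does not settle which model is meant.

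**The section does not strictly contradict itself.** A reader might infer a flat contradiction between the linear and the logistic sentences on methylation. The documents do not establish one. The linear sentence concerns named HPA genes and could take methylation as the outcome; the logistic sentence follows the epigenome-wide analysis and may be a different model. What stands is an unresolved ambiguity.

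**The forest may have a genuine class outcome.** A reader might infer that the Anxiety Factor Score must be dichotomised. The article never names that score as the forest's target. A Mini-DIPS diagnosis is collected at follow-up, and the voting sentence may be a general description of the method. The supportable point is only that the outcome is unnamed and the one defined outcome does not match the description. The efficiency figures do not carry over to the forest. Nor do the documents support saying that forest and linear-model performance cannot be compared: no metric is named and no such comparison is promised.

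**No effective sample size follows.** A reader might turn the loss into a number of participants. The expected rates give 337 × 50% + 788 × 40% ≈ 484, while the Discussion gives 226 + 357 = 583. Neither is the number for the methylation models: these need blood taken at an in-person visit, and the epigenome-wide analysis uses a subset.

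**The main analyses are untouched.** This stands. Stability and cortisol analyses use mixed models, intraclass correlations and correlations, and section 2.9.2 calls the prediction analysis exploratory.

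**Conclusion.** The point holds for section 2.9.4. Logistic regression is specified twice for scores that the plan otherwise analyses as continuous, with no category defined. As written, the models cannot be run without a grouping step that the article does not state. If that step is one binary cut of a roughly normal score, at least about 36% of the information is lost, and an effect with 80% power under linear regression would have about 61% at a median split and 54% at a top-quartile cut. These figures are outside calculations, not the article's; they assume normality, a single cut and, for power, a two-sided 5% level.

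The forest description in section 2.9.2 is a secondary point: its outcome needs to be named.

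Because these analyses are secondary or exploratory, the matter should be fixed but does not put the study's main conclusions at risk.

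**What to change.** **Section 2.9.4.** In both places, replace multiple logistic regression with multiple linear regression on the continuous Linear Deviation Score, Mean Response and CS-Differentiation. For the methylation models, state which variable is the outcome and which the predictor, so that this sentence and the earlier linear-regression sentence can be read together. Keep logistic regression only for a named binary outcome.

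**Section 2.9.2.** If the Anxiety Factor Score is the forest's target, specify a regression forest: tree predictions averaged, with a continuous-error metric in the nested cross-validation and the permutation analysis. If classification is intended, name the binary outcome, for example a Mini-DIPS anxiety diagnosis.

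The change is to wording only. It needs no additional data, visits or resources.

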## Discussion

3

Fear generalization may serve as a transdiagnostic marker of exaggerated defensive responses to stimuli resembling an initial threat condition, but evidence on its stability and role as a risk factor for anxiety is limited. Therefore, the current study aims to clarify several research questions and close these gaps, examining *N* = 226 children (third assessment) and *N* = 357 adults (second assessment) at follow‐up.

Our first question examines the long‐term stability of fear acquisition and generalization. Previous studies have demonstrated fair stability over relatively short to medium time intervals, ranging from 2 weeks to 8 months. Extending this work, our study investigates stability across a substantially longer period of three to 12 years. Given the broad age range, this design allows us to test whether fear acquisition and generalization reflect trait‐like mechanisms. Stable effects would support their role as trait‐like markers and risk factors for pathological anxiety, whereas instability would challenge this assumption. In the case of instability, an important next step would be to identify potential sources of this variability in fear learning, for example, influences of mental health status or dimensional anxiety symptoms. Parallel changes would indicate a state‐like function, suggesting fear generalization reflects dynamic symptom processes rather than a stable predisposition. Conversely, if stability is observed, this would support the interpretation of fear learning as a predictor of anxiety.

The second question addresses predicting later anxiety from fear learning, supplemented by psychometric, life event, (epi)genetic, and stress reactivity data. How molecular and environmental factors shape anxiety is complex, requiring integration of many variables. We will integrate polygenic risk score to capture the genetic liability and to test specific candidate genes for their influence on anxiety levels. By adding targeted DNAm data and environmental factors (e.g., childhood trauma and life events) between the recruitment waves, we construct a comprehensive multilevel model of how fear learning, molecular and environmental factors interact in anxiety. This approach captures the complexity of these processes within the organism. The inclusion of healthy participants allows us to test whether early fear generalization predicts later anxiety outcomes, distinguishing between predictive, non‐predictive, or unsystematic associations with subsequent symptom development. In doing so, this analysis evaluates the extent to which fear generalization functions as a risk marker for anxiety.

The third research question examines links between fear acquisition and generalization and HPA axis activity. HPA‐axis dysregulation is linked to stress‐related disorders including ANX, making these interactions important. Connecting stress responses to fear processes may reveal biological mechanisms underlying anxiety vulnerability and resilience.

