### Test‐Retest Reliability

1.2

Testing whether fear generalization alterations predispose to ANX assumes they are trait‐like, requiring test‐retest reliability (Torrents‐Rodas et al. 2014). For fear acquisition, evidence is mixed (for a summary see Klingelhöfer‐Jens et al. 2022, supplement): early work showed moderate‐to‐strong SCR reliability (Fredrikson et al. 1993), but recent studies report modest and measure‐dependent stability (Klingelhöfer‐Jens et al. 2022). For fear generalization, Torrents‐Rodas et al. (2014) calculated generalizability coefficients (G coefficients) to estimate the proportion of individual variation in responses to CSs and GSs, finding stable individual differences across 8 months in startle, SCRs, and threat expectancy (*R*
_IRS_ = 0.17–0.34) (Torrents‐Rodas et al. 2014). SCRs showed fair reliability in fear acquisition and generalization, while threat expectancy was less consistent over 1–2 weeks (Cooper et al. 2023). Overall, fear generalization shows short‐ and mid‐term reliability, though subjective ratings appear less stable, and long‐term data are lacking.

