
### Fear Acquisition and Generalization Paradigm

2.7

Participants undergo the fear acquisition and generalization paradigm used in earlier assessments (Schiele, Reinhard, et al. 2016), using neutral female faces as conditioned stimuli (03F_NE_C, 10F_NE_C, NimStim Face Stimulus Set; Tottenham et al. 2009). CS+ is paired with a fearful face and aversive scream (International Affective Digitized Sounds, IADS, FemScream2, No. 276; Bradley and Lang 1999), while CS‐ remains unpaired. The experiment includes three phases: pre‐acquisition (unreinforced CS+ and CS‐), acquisition (CS+ reinforced on most trials, while CS‐ remains unpaired), and generalization (CS+, CS‐, and four morphed generalization stimuli, GS1–GS4, with partial CS+ reinforcement). Stimuli are presented with randomized order and intertrial intervals. After each phase, participants rate stimuli on arousal, valence, and US expectancy. An overview of the fear acquisition and generalization paradigm is shown in Figure 3. Compared to earlier assessments, fewer generalization trials are included (see Table 3), with analyses focusing on this first block.

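### A low 3–12-year ICC for the Linear Deviation Score or CS-Differentiation cannot count against a trait without a reliability estimate, and stability alone does not support prediction

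*Protocol article*

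**What the plan says.** The Discussion (section 3) sets the interval, "our study investigates stability across a substantially longer period of three to 12 years", and then says how the result will be read. Stable effects would support a trait-like marker and risk factor, "whereas instability would challenge this assumption". If instability is found, the next step is to look for its sources. The examples named are mental health status and anxiety symptoms. The paragraph closes: "Conversely, if stability is observed, this would support the interpretation of fear learning as a predictor of anxiety".

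Section 2.9.1 plans mixed models, a variance component analysis and two coefficients on responses to the stimuli: R_IRS for stability of the response pattern, and R_C, "which measures the reliability of change in responses across individuals between timepoints". For the summary indices it plans "ICCs based on the Linear Deviation Score, the Mean Response across all stimuli", and CS-Differentiation. All three ICCs compare sessions.

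Section 1.2 treats retest reliability as something that must hold before a predisposition can be tested. It cites earlier work with R_IRS of 0.17–0.34, described as "finding stable individual differences across 8 months in startle, SCRs, and threat expectancy". A second study found fair reliability for SCR, "while threat expectancy was less consistent over 1–2 weeks".

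The Limitations (3.1) concede that trait and state cannot be fully separated. The reasons given there are current symptom status, habituation, varying intervals and developmental stage. Measurement error is not among them.

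**The concern.** Objective 1 asks whether fear acquisition and generalization are stable. A between-session ICC falls below 1 for two reasons: the person's true standing has moved, or the index measures that standing imprecisely. LDS and CS-Differentiation are contrasts between stimuli, and contrasts often carry more error than the responses they are built from. If a low ICC is read as a challenge to the trait assumption, a noisy index and a real change lead to the same conclusion.

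The closing sentence raises a different problem. It takes stability of the predictor as support for its predictive role, although the article gives that question to a separate analysis.

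**Working it through.** **The article's own figure.** The only numerical benchmark for pattern stability is R_IRS 0.17–0.34 over 8 months (section 1.2). It cannot be reproduced, because its variance components are not given. It is also a different coefficient from an ICC of LDS, so it is context and not calibration. No cut-off for stable or unstable is stated.

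**Low stability.** Assume classical test theory, with equal reliability and equal variance at both sessions:

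observed stability = true stability × √(rel₁ × rel₂), so true stability = observed ÷ reliability.

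The reliabilities below are assumptions. For an observed value of 0.25:

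| Assumed reliability | Implied true stability |
|---|---|
| 0.25 | 0.25 / 0.25 = 1.00 |
| 0.3 | 0.25 / 0.3 = 0.83 |
| 0.5 | 0.25 / 0.5 = 0.50 |
| 0.8 | 0.25 / 0.8 = 0.31 |
| 0.9 | 0.25 / 0.9 = 0.28 |

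A simulation with 200,000 draws agrees. A perfectly stable trait with reliability 0.25 gives an observed correlation of 0.251. A largely state-like process (true stability 0.31, reliability 0.80) gives 0.252.

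**Sample size does not resolve this.** With Fisher's z, the 95% interval is tanh(atanh(0.25) ± 1.96/√(N−3)). At the Discussion's N = 226 it is 0.12 to 0.37, and at N = 357 it is 0.15 to 0.34. Both explanations give the same interval.

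**Is low reliability plausible?** Take CS-Differentiation as CS+ minus CS−; the article does not print the formula. With equal variances, the reliability of a difference is (rel − r)/(1 − r), where r is the correlation between the two responses. With rel = 0.8 and r = 0.7 it is 0.1/0.3 = 0.33. With rel = 0.7 and r = 0.6 it is 0.1/0.4 = 0.25. With rel = 0.8 and r = 0.3 it is 0.5/0.7 = 0.71. So it may be low or adequate, and only data can tell.

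**What the variance components and R_C add.** With stimuli as replicates, a person's overall change between sessions can be separated from error. Change in the generalization pattern is the person × stimulus × session term. With one value per stimulus per session, that term is the residual. Section 2.7 says "After each phase, participants rate stimuli on arousal, valence, and US expectancy" and does not give the number of ratings; if it is one, pattern change in ratings cannot be separated from error. Section 2.7.2 averages SCR per stimulus. If SCR trials were modelled singly, error could be separated for those responses. In either case LDS and CS-Differentiation receive only the ICC.

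**High stability and prediction.** Take three variables: the index at baseline, the index at follow-up, and later anxiety. Stability 0.9 with zero correlation to anxiety is a valid correlation matrix (eigenvalues 0.1, 1.0, 1.9). Observed stability 0.25 with correlation 0.3 to anxiety is also valid (eigenvalues 0.68, 0.75, 1.57). Stability therefore does not settle prediction in either direction.

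**The case against.** The other side has good points.

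- **The wording is conditional.** The paragraph is Discussion text, with no threshold and no formal decision. After instability it calls for a search for sources. This stands, and it limits the point to interpretation. Even so, the sources it names are substantive ones, and noise is not mentioned.
- **Safeguards exist.** The variance components and R_C are meant to show how much non-stable variance is systematic. For stimulus-level responses this stands in part. It does not carry over to the derived indices.
- **Youths have three waves.** Under strong assumptions about the form of change and equal reliability, three waves can help to separate reliability from stability. The article states no such use, and adults have two timepoints.
- **Prediction is tested separately.** Section 2.9.2 adjusts for baseline anxiety, and the Discussion allows for a non-predictive result. This stands: an unrelated index should be identified there. What remains is one sentence that claims too much.

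A reader might infer three stronger things that the documents do not support. First, that a missing reliability estimate also undermines a high-stability result: it does not, because observed stability cannot exceed √(rel₁ × rel₂), so a high value itself shows adequate reliability. Second, that 0.17–0.34 shows LDS to be noisy: that range is R_IRS, and the article calls it stable. Third, that a stable trait would be formally declared unstable: no rule or cut-off in the article does so.

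**Conclusion.** The point holds for the derived indices. A low between-session ICC for LDS or CS-Differentiation, taken alone, is inconclusive about a trait. Under the assumed reliabilities of 0.3 to 0.8, an observed 0.25 is compatible with true stability from about 0.83 down to 0.31. The article supplies none of these reliabilities, so the range shows how wide the ambiguity could be and does not estimate it.

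The stability-to-prediction sentence fails on separate, logical grounds. Section 1.2 makes stability a precondition, and only the prediction analysis can show prediction.

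No planned analysis is wrong. What changes is what Objective 1 can conclude if stability turns out low.

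**What to change.** 1. Report odd-even (split-half) reliability of the SCR-based LDS and CS-Differentiation at each wave, stepped up to full length. Interpret the long-term ICC against it. Read a low ICC as evidence against a trait only where reliability is adequate, and otherwise as inconclusive. Table 3 must be reconciled first: the earlier-wave generalization blocks are stated as 36 trials, but the items sum to 6 + 6 + 6 + 12 + 12 + 12 = 54, and reliability depends on the number of trials.
2. For ratings, compare generalization block 1 with block 2 at A-T1/1 and C-T1 only, where Table 3 shows no de-generalization phase in between, and only if ratings were taken after each block. This is an approximate benchmark, because learning continues between blocks. Follow-up has no block 2. If block-wise ratings do not exist, state that a low rating-based ICC cannot separate noise from change.
3. Reword the last sentence of the Discussion paragraph so that stability is a precondition and the predictor claim rests on section 2.9.2.
4. Name measurement error in the Limitations.

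The cost is a little extra analysis of trial-level and block-level data, with no new data collection. Any reliability-corrected ICC will have a wider interval, and conclusions will be less definite where reliability is low.
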